### Economic evaluation

The economic evaluation will be performed alongside the clinical trial. The aim of the economic evaluation is to relate the incremental costs of immediate tubal flushing at HSG with oil-based contrast during the initial fertility work-up (intervention group) in comparison with delayed tubal flushing at HSG with oil-based contrast six months after completing the fertility work-up (control group) to the incremental health effects. The cost-effectiveness analysis will be performed from a societal and healthcare perspective according to Dutch guidelines with a time horizon of twelve months [18]. Costs will be measured from a societal perspective using web-based questionnaires consisting of the iPCQ and iMCQ at six and twelve months of follow-up. Cost categories that will be included are: healthcare costs, loss of productivity costs and patient costs (care services paid for by the patients themselves). The healthcare costs include the costs made to achieve conception leading to a live birth and costs for pregnancy and delivery. The statistical analyses will be done according to the intention-to-treat principle. Incremental cost-effectiveness ratios (ICERs) will be calculated by dividing the difference in the mean total costs between the treatment groups by the difference in mean effect between the treatment groups.

Subsequently, a budget impact analysis will be conducted. The data from the clinical study and the cost-effectiveness analysis regarding the differences in costs and health outcomes will be combined with national prevalence and incidence data to extrapolate the findings to a time horizon of 5 years. The economic analysis will be reported in a separate paper.

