### Outcomes

The primary outcome is time to conception leading to live birth, with the first day of the last menstrual bleeding before a positive pregnancy test within 12 months after randomization. We will assess the presence of this endpoint also at six months after randomization as a co-primary outcome. All outcomes are listed and described in Table 1.

**Table 1 Tab1:** Outcomes and descriptions

**Primary outcome**	**Definition/measurement**
Time to conception leading to live birth measured at 6 months	Calculated from the first day of the last menstrual bleeding before a positive pregnancy test
Time to conception leading to live birth measured at 12 months	Calculated from the first day of the last menstrual bleeding before a positive pregnancy test
**Secondary outcome**	**Definition/measurement**
Biochemical pregnancy	A positive pregnancy test or serum HCG-level greater than 5 IU/L
Clinical pregnancy	Gestational sac visible on ultrasonography
Ongoing pregnancy	Positive heartbeat at 12 weeks of pregnancy on ultrasonography
Miscarriage	Non-vitality on ultrasound or spontaneous loss of pregnancy
Ectopic pregnancy	No intrauterine gestational sac with an ectopic gestational sac and/or persistent serum HCG levels
Multiple pregnancy	Pregnancy of two or more fetuses
Complications after HSG	All adverse events occurring within one month after HSG procedure, for example pelvic infection, intravasation and allergic reaction
Level of pain during HSG	Reported on VAS (scores: 0.0 to 10.0 cm)
Thyroid function after HSG	Serum FT4 and TSH one month after HSG
Used fertility treatments	IUI, IVF, ICSI
Pregnancy complications	E.g. pregnancy induced hypertension, gestational diabetes, still birth
Pregnancy outcomes	E.g. gestational age, pre-term birth, birth weight
Cost-effectiveness	Effectiveness: time to conception leading to live birth Costs: Healthcare perspective: costs for HSG and fertility treatments Societal perspective: healthcare costs, loss of productivity costs and patient costs (care services paid for by the patients themselves) using iMCQ and iPCQ

HCG: human chorionic gonadotropin, HSG: hysterosalpingography. VAS: Visual Analogue Scale, FT4: free thyroxine, TSH: thyroid-stimulating hormone, IUI: intrauterine insemination, IVF: in vitro fertilization, ICSI: intracytoplasmatic sperm injection, iMCQ: Medical Consumption Questionnaire, iPCQ: Productivity Cost Questionnaire

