### Follow-up

For the primary study, we will follow-up women for twelve months, with conception rates assessed six and twelve months after randomization. For each conception within twelve months after randomization, we will assess whether this conception leads to live birth beyond the twelve months window. Follow-up outcome data will be extracted from women’s medical records and/or by sending a digital questionnaire send to them through Castor EDC. The follow-up data include information about fertility treatments (used to calculate direct medical costs), (ongoing) pregnancy(ies) and delivery if applicable. At six and twelve months after randomization women will receive a digital questionnaire send through Castor EDC to explore indirect costs from a societal perspective during the preceding six months (iMCQ [16] and iPCQ [17]). Table 2 provides an overview of the study activities. For a secondary analysis, we will follow women until 36 months after randomization.

**Table 2 Tab2:** SPIRIT schedule of enrollment, intervention and assessments

	Study period					
	Enrollment	Allocation	Post-allocation			
TIMEPOINT	-t_1_	t_0_	t_1_	t_2_	t_3_	t_4_
ENROLLMENT:						
Eligibility screening	X					
Informed consent	X					
Allocation		X				
INTERVENTIONS:						
Immediate oil-HSG			X			
Delayed oil-HSG				X		
ASSESSMENTS:						
Baseline characteristics		X				
APAIS questionnaire*			X or X			
Pain score*			X or X			
HSG procedure, results and complications*			X or X			
iMCQ				X	X	
iPCQ				X	X	
Fertility treatment					X	
Pregnancy yes/no				X	X	
Ongoing pregnancy outcome						X

*Depending on the allocated intervention. -t_1_: prior to allocation, t_0_: at allocation, t_1_: first menstrual cycle after allocation, t_2_: 6 months after allocation, t_3_: 12 months after allocation, t_4_: 2 months post-partum

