There is limited literature on the therapeutic role of HSG during fertility work-up in women with unexplained infertility. While two randomized controlled trials with small sample sizes have demonstrated a positive effect of tubal flushing during HSG with oil-based contrast on pregnancy rates compared to no tubal flushing in women with unexplained infertility, information on live birth rates and time to pregnancy was not investigated [21, 22]. Recently, a Dutch controlled cohort study compared pregnancy rates after an extensive fertility work-up and a concise (standard) fertility work-up [23]. The concise fertility work-up included inventory of the medical history, physical examination, transvaginal ultrasound and semen analysis. Other tests were performed if indicated. Extensive work-up included the elements of the concise work-up plus cycle monitoring, Chlamydia antibody determination, postcoital test and tubal patency testing by HSG. After follow-up of twelve months the ongoing pregnancy rate for couples who underwent the extensive fertility work-up was significantly higher compared to the couples who underwent the concise fertility work-up (59% vs. 47%; p < 0.001). HSG was performed significantly more often during the extensive fertility work-up than during the concise fertility work-up (42% vs. 33%; p < 0.001) and HSG was often performed within the first six months after start of the fertility work-up. In couples who underwent the extensive fertility work-up the time to pregnancy was shortened as well. These findings support our hypothesis that immediate HSG incorporated in the fertility work-up may improve fertility outcomes [23].

Worldwide health care costs are increasing [24]. When incorporating HSG with oil-based contrast as standard part of fertility work-up the additional costs need to be considered as well. Therefore, we will perform a cost-effectiveness analysis alongside the proposed study, considering the costs from a healthcare (costs for tubal patency testing and for fertility treatments) and societal perspective. The costs from a societal perspective will be estimated using validated questionnaires (iMCQ and iPCQ [16, 17]) to assess absenteeism, productivity loss and medical consumption.

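### The economic evaluation stops costs at month 12 but counts births up to about month 21, and the article disagrees with itself on whether pregnancy and delivery costs are in scope

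*Protocol article*

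**What the plan says.** The Economic evaluation section fixes three things on the cost side.

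- **Horizon:** the analysis is done "according to Dutch guidelines with a time horizon of twelve months".
- **Measurement:** societal costs are collected "using web-based questionnaires consisting of the iPCQ and iMCQ at six and twelve months of follow-up".
- **Content:** "The healthcare costs include the costs made to achieve conception leading to a live birth and costs for pregnancy and delivery".

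On the effect side, the cost-effectiveness row of Table 1 (Outcomes) reads "Effectiveness: time to conception leading to live birth". Table 1 dates conception as "Calculated from the first day of the last menstrual bleeding before a positive pregnancy test". The Follow-up section adds that, for conceptions within twelve months, "we will assess whether this conception leads to live birth beyond the twelve months window".

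Two other places give a narrower cost scope. Table 1 has "Healthcare perspective: costs for HSG and fertility treatments", and the Discussion describes the analysis as "considering the costs from a healthcare (costs for tubal patency testing and for fertility treatments) and societal perspective". Neither names pregnancy or delivery.

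The Follow-up section also says that delivery information is extracted from records or questionnaires, and Table 2 has a contact two months post-partum. Of the follow-up data, only the fertility treatments are tied to direct medical costs.

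**The concern.** Costs and effects are cut at different times. A conception in month 11 earns full credit as an effect once the child is born, but its delivery falls around month 20, outside the cost horizon. A conception in month 1 earns the same credit and its delivery is costed. Whether a birth carries a delivery cost therefore depends on how early the woman conceived, and earlier conception is the effect under test. The truncation cannot be assumed to cancel between arms.

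The incremental cost and the ICER would be affected, and so would the five-year budget impact analysis, which reuses the cost differences. The article's conclusion names cost-effectiveness as one of the grounds on which guidelines might change. The primary clinical comparison is not affected.

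The conflict over scope comes first: until it is settled, a reader cannot tell whether delivery costs enter the healthcare perspective at all.

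**Working it through.** **Inputs from the article (Sample size section):** control median 11 months; expected control rate 53%; hazard ratio 1.39; 554 women allocated 1:1, so 277 per arm. **Assumed here:** constant hazard, and delivery 40 weeks (280 days) after the last menstrual period.

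**1. Reproduce the planning figure.** The control hazard is ln 2 / 11 = 0.0630 per month. By month 12, 1 − exp(−0.0630 × 12) = 53.1%, which matches the stated 53%. The immediate-arm hazard is 0.0630 × 1.39 = 0.0876, giving 1 − exp(−0.0876 × 12) = 65.0%. The difference is 12.0 points.

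**2. Find which conceptions deliver inside the horizon.** 280 / 30.44 = 9.2 months, so the last menstrual period must fall by month 12 − 9.2 = 2.8. The latest counted birth comes at about 12 + 9.2 = month 21.

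**3. Compare births costed with births counted.**

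| | Control | Immediate | Difference |
|---|---|---|---|
| Delivery by month 12: 1 − exp(−hazard × 2.8) | 16.2% | 21.8% | 5.6 points |
| Birth counted as effect | 53.1% | 65.0% | 12.0 points |
| Share of counted births after month 12 | 69.5% | 66.5% | |

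Pooled, 1 − (16.2 + 21.8) / (53.1 + 65.0) = 68%. That is about 222 of 327 expected births.

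**4. Vary the assumptions.** The pooled share is 66% at 39 weeks and 63% at 38 weeks. If conceptions are spread evenly over the year it is 9.2 / 12 = 77%. With a Weibull hazard passing through the same 12-month rate it is 75% (shape 1.2), 59% (0.8), 53% (0.7) and 47% (0.6).

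**5. Direction if flushing only brings conception forward.** Suppose both arms end with the same number of births. The true difference in delivery cost is then zero. Deliveries inside the horizon depend only on the first 2.8 months. With the effect starting at randomization, the immediate arm is charged for 5.6 points more deliveries (about 15 women of 277). The Description of intervention section places HSG preferably in the month after randomization, so a lag is realistic. With a lag L, the immediate-arm share is 1 − exp(−0.0630 × [L + 1.39 × (2.8 − L)]):

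- L = 0.5 month: 20.8%, a gap of 4.6 points.
- L = 1 month: 19.8%, a gap of 3.6 points.

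**6. Direction if the hazard ratio of 1.39 holds for all twelve months.** The true difference in births is 12.0 points, and only 5.6 of them have a delivery inside the horizon. The immediate arm's extra delivery cost is understated by a little more than half.

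**The case against.** The strongest reply is that the article does not say that later deliveries go uncosted. The effect is also labelled as within twelve months and yet is followed to birth, so the twelve-month horizon could likewise mean pregnancies conceived within twelve months. Delivery data are collected, a post-partum contact exists, and the economic analysis is to be reported in a separate paper, whose plan may settle the boundary. Part of this stands: the authors may intend to cost those deliveries, and the two-thirds figure describes the literal reading. But the article does more than leave a detail open. It states a horizon, the questionnaire times, the cost items and the effect, and taken together these do not fit.

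A second reply is that Table 1 and the Discussion keep pregnancy and delivery out of the healthcare perspective, so the mismatch shown here would not arise there. That also stands. It does not remove the point, because the Economic evaluation section says the opposite and nothing says which governs.

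A reader might infer that the twelve-month rule simply penalizes immediate flushing. The documents do not support that. It holds for a pure timing gain, but the equal-births case departs from the article's planning assumptions. Under the planned hazard ratio held throughout, the rule favours the immediate arm by leaving out more than half of its extra delivery cost. Nor can the distortion be put in money, since the article gives no unit costs.

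**Conclusion.** The point holds as an unreconciled boundary and an unreconciled cost scope in the economic evaluation. On the literal reading, about two thirds of counted births fall outside the cost window. The 68% rests on a constant hazard and 40 weeks' gestation; the share stays between 47% and 77% across the variants tried. The resulting error in the incremental cost can go either way. Deliveries would be overcharged to the immediate arm by about 3.6 to 5.6 points if flushing only accelerates conception, or undercounted (5.6 of 12.0 points) if the planned hazard ratio persists for twelve months. The effect pattern is unknown in advance, so the bias cannot be signed or corrected afterwards without costs followed to the end of pregnancy. This concerns a secondary outcome, but one that the article links to guideline change, so it should be corrected before the economic analysis is run.

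**What to change.** State one cost scope and use it in Table 1, the Economic evaluation section and the Discussion.

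If pregnancy and delivery costs are in scope, define the cost boundary by conception, as for the effect: for every conception dated within twelve months of randomization, follow these costs to the end of that pregnancy in both arms, including after month 12. Apply unit costs to the delivery data already being extracted and to the contact two months post-partum. Show an alternative analysis that leaves pregnancy and delivery costs out of both arms.

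The cost is revised wording, some extra unit-cost work, and economic results that wait for the last counted birth. The primary outcome has to wait for those births anyway.

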### Data management and monitoring

Study data will be collected in the web-based application Castor EDC, using allocated, anonymous randomization numbers for each participant. Only local investigators have access to the key document with the linkage of the randomization number and personal data.

An interim analysis is not planned. Suspected unexpected serious adverse reactions (SUSARs) and severe adverse events (SAEs) will be reported to the sponsor and the sponsor will report them through the Dutch web portal ToetsingOnline to the accredited Medical Ethics Committee (IRB) of Amsterdam UMC, location Vrije Universiteit Amsterdam. We will report SAEs which occur within one month after the HSG procedure and congenital anomalies and birth defects. All adverse events (AEs) directly related to the HSG procedure will be reported and followed until they have abated or until a stable situation has been reached. Yearly, a safety report will be submitted to the IRB of Amsterdam UMC, location Vrije Universiteit Amsterdam, which consists of all the suspected SAEs and a report concerning the safety of the subjects.

A data safety monitoring board will not be installed since the product and intervention used in this study are registered for the given indication and have been used in clinical practice for decades.

Monitoring will be performed by an independent monitor (Clinical Monitoring Center, Amsterdam UMC) according to Good Clinical Practice guidelines. The monitor will have access to the data and source documents of the trial. Signed informed consent forms are stored in the local participating centers, all forms and study data will be archived for at least 25 years in the participating centers according to national regulations.

## Discussion

The role of HSG during the fertility work-up and the subsequent treatment advice in women with unexplained infertility varies between guidelines worldwide. Table 3 represents an overview of different international guidelines for tubal patency testing and treatment for couples with unexplained infertility. In these guidelines HSG is currently used as a diagnostic tool for assessing tubal patency, without considering the established fertility enhancing effect of tubal flushing during HSG. Additionally, these guidelines do not specify the type of contrast to be used during HSG.

**Table 3 Tab3:** Overview of the guidelines for unexplained infertility in the United Stated, the United Kingdom and the Netherlands

Guideline	Tubal patency test		Treatment
	Low risk for tubal pathology	High risk for tubal pathology	
ASRM, the United States (5)	HSG	HSG	3–4 Cycles of hormonal stimulated IUI before starting IVF
NICE, the United Kingdom (4)	HSG	Laparoscopy	In total 2 years of regular unprotected intercourse before starting IVF
NVOG, the Netherlands (6)	No tubal patency test	HSG	Favorable chance to conceive (> 30%, based on the Hunault prediction score(14)) within 1 year: 6–12 months expected management, before start of 6 cycles hormonal stimulated IUI followed by IVF. Unfavorable chance (< 30%): 6 hormonally stimulated IUI cycles followed by IVF

ASRM: American Society for Reproductive Medicine, NICE: National Institute for Health and Care Excellence, NVOG: the Netherlands Society of Obstetrics and Gynaecology Global Network, IUI: intrauterine insemination, IVF: in vitro fertilization

The H2Oil-timing study will provide insight into whether HSG with oil-based contrast should be incorporated as a therapeutic procedure during the initial fertility work-up in women with unexplained infertility. If incorporating HSG with oil-based contrast as standard part of the fertility work-up leads to a shorter time to conception and higher live birth rate, fewer couples will need costly fertility treatments. This is particularly significant since fertility treatments are known to cause substantial psychological burden to infertile couples[19, 20].

There is limited literature on the therapeutic role of HSG during fertility work-up in women with unexplained infertility. While two randomized controlled trials with small sample sizes have demonstrated a positive effect of tubal flushing during HSG with oil-based contrast on pregnancy rates compared to no tubal flushing in women with unexplained infertility, information on live birth rates and time to pregnancy was not investigated [21, 22]. Recently, a Dutch controlled cohort study compared pregnancy rates after an extensive fertility work-up and a concise (standard) fertility work-up [23]. The concise fertility work-up included inventory of the medical history, physical examination, transvaginal ultrasound and semen analysis. Other tests were performed if indicated. Extensive work-up included the elements of the concise work-up plus cycle monitoring, Chlamydia antibody determination, postcoital test and tubal patency testing by HSG. After follow-up of twelve months the ongoing pregnancy rate for couples who underwent the extensive fertility work-up was significantly higher compared to the couples who underwent the concise fertility work-up (59% vs. 47%; p < 0.001). HSG was performed significantly more often during the extensive fertility work-up than during the concise fertility work-up (42% vs. 33%; p < 0.001) and HSG was often performed within the first six months after start of the fertility work-up. In couples who underwent the extensive fertility work-up the time to pregnancy was shortened as well. These findings support our hypothesis that immediate HSG incorporated in the fertility work-up may improve fertility outcomes [23].

Worldwide health care costs are increasing [24]. When incorporating HSG with oil-based contrast as standard part of fertility work-up the additional costs need to be considered as well. Therefore, we will perform a cost-effectiveness analysis alongside the proposed study, considering the costs from a healthcare (costs for tubal patency testing and for fertility treatments) and societal perspective. The costs from a societal perspective will be estimated using validated questionnaires (iMCQ and iPCQ [16, 17]) to assess absenteeism, productivity loss and medical consumption.

As shown in Table 3, contrary to elsewhere, initiation of active fertility treatment for couples with unexplained infertility in the Netherlands is based on their prognosis for natural conception (using the prognostic model of Hunault [14]). Shingshetty et al. emphasizes the importance of a prognosis-based approach to couples with unexplained infertility to find balance between overtreatment and give access to treatment for those who benefit from it [25]. When interpreting the results of the H2Oil-timing, its consideration is required that the results of this study might not be directly applicable to guidelines which do not distinguish between a favorable and non-favorable prognosis to conceive naturally.

The safety of HSG with oil-based contrast is extensively described in a recent systematic review including all the published evidence since the 1920’s [26]. The most frequently reported complications after HSG with oil-based contrast are intravasation and infection. Intravasation occurred significantly more frequent after the use of oil-based contrast compared to the use of water-based contrast (3% vs. 2%; OR 5.05 95% CI 2.3–11.2; p < 0.0001), without cases of serious lasting consequences. To minimize the risk of formation of oil-embolism in the H2Oil-timing study, the HSG procedure will be immediately discontinued if intravasation is noticed. The incidence of pelvic infection after 1960 was 0.6% after oil-based contrast (95% CI 0.2-1.0) compared to 0.4% (95% CI 0.0-7.3) in the water-based group [26]. According to the recent published Cochrane systematic review it is uncertain whether tubal flushing with oil-based contrast increases the risk of infection due to very low quality of evidence [12]. In the H2Oil-timing study antibiotic therapy will be prescribed in cases of suspected intra-abdominal adhesions or hydrosalpinges. In the literature, concerns about maternal and neonatal thyroid dysfunction after HSG with oil-based contrast are reported as well. Several studies have shown that an iodine excess in urine was detected in the majority of the women after HSG with oil-based contrast which lasted for at least 12 to 24 weeks with a peak concentration by four weeks, leading to a prevalence of subclinical hypothyroidism of approximately 20% [27, 28]. Mekaru et al. showed that women with subclinical hypothyroidism before HSG were more at risk to develop hypothyroidism after HSG, compared to euthyroid women [29]. It is reassuring that recent studies have shown that preconceptional exposure to oil-based contrast during HSG did not increase the risk for thyroid dysfunction in offspring [27, 30, 31]. In the H2Oil-timing study women with thyroid dysfunction can only be included if their TSH serum concentration is below 2.5 mU/L, to prevent further exacerbation of the thyroid dysfunction.

In conclusion, if this study shows that tubal flushing with oil-based contrast incorporated during the initial fertility work-up reduces time to conception and is a cost-effective strategy, the results may lead to adjustments of (inter)national guidelines and change practice.

